**Figure 1 F1:**
[figure not shown]
Study design.

Individuals randomized to the BI group receive screening, a single-encounter BI with referral to treatment when indicated, and a single follow-up phone contact approximately one week later. Individuals assigned to ECAU receive screening, a handout with the results of their drug screen, the risk associated with their drug use, and a list of referrals to chemical dependency treatment. Individuals in both groups are re-assessed at 3, 6, 9, and 12 months after baseline. All assessments are carried out in person wherever possible, with phone interview as a back-up option. Persons conducting follow-up assessments are blinded to the participant’s intervention versus control group assignment.

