### Specific nature of the intervention

The study employed a total of 17 interventionists. We decided to have social workers who were already employed in each of the clinics conduct the BI as they were more available and less costly than primary care physicians. We began with eight social workers and, as the study evolved, required additional interventionists. We recruited three additional social workers who were working in the clinics, two social workers not working in the clinics, two clinical psychology doctoral students, and two bachelor-level individuals with experience conducting structured clinical interviews.

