### Data analysis

Analyses will compare outcomes for the BI and ECAU groups following the intent-to-treat principle. If indicated, these models will take into account baseline differences between the two groups. Time trend models will be used to examine temporal effects, specifying time of assessment as a categorical variable (baseline, 3, 6, 9, and 12 months). Because assessments are nested within patients and patients are nested within clinics and interventionists, analyses will be conducted with linear mixed models. Clinics will be treated as fixed effects, as they were purposively sampled. In contrast, interventionists were assigned to patients based on availability when a BI had to be administered. For interventionists, random effects will therefore be specified and tested.

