#### Power analysis

Power analyses were conducted with PASS software version 08.0.5 [61]. For the primary outcome of drug use reduction, we computed power for the last point in time when data are collected from participants. We expect to enroll 1,000 study participants, 500 each per BI and ECAU group. Assuming an overall response rate of 75%, we would have data from 375 individuals per group at 12 months. According to results from the WASBIRT study, the frequency distribution of number of days drugs were used in the past 30 days follows a Poisson distribution. For individuals who received a BI in WASBIRT, at baseline, average days of drug use in the past 30 days were 3.8 for moderate risk users, 7.0 for high risk users who received only a BI, and 8.7 for high risk users who received a BI and brief therapy and/or chemical dependency treatment. Based on these averages, the study would have 89% power to detect as low as a 2.5% reduction in average drug use days for moderate risk users, at a two-sided alpha level of .05, and an R^2^ between BI indicator variable and other covariates of .25. If the R^2^ between the BI indicator variable and other covariates were 0.5 (a conservative assumption), the power to detect as low as a 2.5% reduction in average drug use days for moderate risk users is 74%; the power to detect a 5% reduction in average drug use days is 99%. For high risk users, the power to detect a reduction in drug use of at least 2.5% is higher. The end-status analysis assumed for these power calculations is considerably conservative, as data from earlier points in time are not used. Thus, the proposed study has sufficient power to address the first two specific aims.

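### Only BI patients have an interventionist, but the model text neither limits the random effect to the BI arm nor commits to keeping it, and the stated power has no term for this clustering

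*Protocol article*

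**What the plan says.** The Data analysis section of the protocol article explains the choice of model: "Because assessments are nested within patients and patients are nested within clinics and interventionists, analyses will be conducted with linear mixed models". Clinics are fixed effects. On interventionists it notes that "interventionists were assigned to patients based on availability when a BI had to be administered" and concludes: "For interventionists, random effects will therefore be specified and tested". It does not say what happens to the term after the test, or how ECAU patients enter it.

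The Study design section (text below Figure 1) describes the control arm: "Individuals assigned to ECAU receive screening, a handout with the results of their drug screen", together with risk information and a referral list. No interventionist is involved. Under Specific nature of the intervention: "The study employed a total of 17 interventionists". Eight began and the others joined later.

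The Power analysis section states: "We expect to enroll 1,000 study participants, 500 each per BI and ECAU group". With 75% response this leaves 375 per group at 12 months. From a Poisson distribution with a mean of 3.8 days for moderate risk users, it gives 89% power for a 2.5% reduction (R² = .25), 74% for the same reduction (R² = .5) and 99% for a 5% reduction (R² = .5). It mentions no ICC, number of interventionists or design effect, and judges power sufficient for the first two aims.

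**The concern.** The stated nesting covers all patients, but by the article's own description it exists in one arm. Variance between interventionists should enter the standard error of the BI-versus-ECAU difference through the BI arm only. A model that omits it gives standard errors that are too small. A power calculation that omits it is too favourable.

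The effect is not far-fetched here. The section on the intervention expects MI skill to vary enough to be analysed, and Aim 2 asks whether fidelity goes with better outcomes. If it does, and fidelity differs between interventionists, BI outcomes cluster by interventionist. Clinic fixed effects common to both arms do not remove that variance.

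**Working it through.** **Inputs.** From the article: 375 per arm at 12 months, 17 interventionists, mean 3.8 days, two-sided alpha .05, R² of .25 or .5. Assumed: ICC of .01, .02 and .05 (the article gives none) and equal caseloads.

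**Step 1, the stated power.** Wald test on the log rate ratio b, with variance [1/(375 × 3.8) + 1/(375 × 3.8 × (1 − reduction))]/(1 − R²), and power = Φ(|b|/SE − 1.960).
- 2.5% reduction, R² = .25: variance = (.000702 + .000720)/.75 = .001895, SE = .0435, |b| = .0253, ratio .582, power 8.4%.
- 2.5%, R² = .5: 6.9%.
- 5%, R² = .5: 15.8%.

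Multiplying the mean by a further 30 gives 89.0%, 73.9% and 99.95%, which matches the stated 89%, 74% and 99%. The match needs no clustering term, so none is in the stated figures.

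**Step 2, design effect in the BI arm.** Patients per interventionist: m = 375/17 = 22.06. Design effect DE = 1 + (m − 1) × ICC. With clustering in one arm only, the variance of the difference is multiplied by (DE + 1)/2.

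**Step 3, effect on the stated power.** New power = Φ[(1.960 + z)/√((DE + 1)/2) − 1.960], with z = 1.227 for 89% and 0.643 for 74%.

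| Assumed ICC | DE, BI arm | SE multiplier | 89% becomes | 74% becomes |
|---|---|---|---|---|
| .01 | 1.21 | 1.05 | 86% | 70% |
| .02 | 1.42 | 1.10 | 83% | 66% |
| .05 | 2.05 | 1.24 | 73% | 56% |

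Example at ICC .05: 3.186/1.236 − 1.960 = 0.62, and Φ(0.62) = 73%. Unequal caseloads lower this further: with an assumed coefficient of variation of 0.6, DE is 2.45 and 89% becomes 68%. From the uncorrected-for-exposure base of 8.4% in step 1, the same design effects give 8.0%, 7.6% and 6.8%.

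**Step 4, the test of the random effect.** F-test with 16 and 358 degrees of freedom at 5%, with the F ratio scaled by 1 + m × ICC/(1 − ICC). Detection probability: 15.5%, 30.5% and 71.6% for ICC .01, .02 and .05.

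**Step 5, consequence of the choice after the test.** Simulation under no treatment effect (17 clusters of 22 against an unclustered control arm, 20,000 trials per ICC, run twice independently):
- Term dropped when not significant: type I error 5.6%, 6.4% and 5.7% in one run, and 5.7%, 6.0% and 6.1% in the other (ICC .01, .02, .05).
- Term kept, BI arm only: between 4.4% and 5.2% throughout.

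**The case against.** The strongest reply is that the plan already contains the interventionist effect and links it to delivery of a BI. The general nesting sentence explains why mixed models are used and is not a model equation. The coding of ECAU patients and the degrees of freedom are matters an article may leave to the analysis plan. This largely stands, and it limits the point.

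Three stronger readings are tempting, and the article supports none of them.
- A reader might infer that the standard errors are wrong. They are not, if the term is confined to BI patients and kept.
- A reader might cite the type I error when clustering is ignored: 6.2%, 7.5% and 11.3% at ICC .01, .02 and .05. The plan does not ignore it. Nor does it state that a non-significant term is dropped. Even on that reading the excess is about one percentage point, because the clustering that does most harm (ICC .05) is also the clustering the test usually finds.
- A reader might suppose that ECAU is coded as one further interventionist level, which would inflate the standard error greatly. The article nowhere proposes this.

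What the reply does not answer is the power statement. It is a figure in the article, with a conclusion drawn from it, and it treats patients as independent although the planned model does not. It is also fair to say that the exposure problem in the base calculation is much larger. That does not remove this point: a corrected calculation still needs the design effect.

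**Conclusion.** The point holds as a gap in the model statement and an overstatement of power. The article neither limits the interventionist effect to the BI arm nor commits to keeping it. The likely harm to type I error from testing and dropping is small, about 5.6 to 6.4% against 5%.

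The stated power is optimistic for any ICC above 0. The loss from 89% is about 3 points at ICC .01, 6 to 7 at .02 and 16 at .05. These sizes rest on assumed ICCs, equal caseloads and a normal approximation. They are relative to stated figures that themselves arise only with the extra factor of 30; without it the base is about 8%, 7% and 16%.

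**What to change.** In Data analysis, state that the interventionist random effect applies to the BI arm only (a random coefficient on the BI indicator, zero for ECAU), with arm-specific residual variance; that it is kept whatever its p-value; and that inference uses Satterthwaite or Kenward-Roger degrees of freedom. The variance estimate can still be reported and tested for description.

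In Power analysis, first correct the base calculation so that the 30-day mean is not multiplied again by 30. Then multiply the BI-arm variance by 1 + (22 − 1) × ICC, show the result for ICC .01 to .05, and revisit the claim of sufficient power.

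The cost is a few sentences, slightly wider intervals and a lower stated power. No change to data collection is needed beyond recording which interventionist saw each BI patient.

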#### Power analysis

Power analyses were conducted with PASS software version 08.0.5 [61]. For the primary outcome of drug use reduction, we computed power for the last point in time when data are collected from participants. We expect to enroll 1,000 study participants, 500 each per BI and ECAU group. Assuming an overall response rate of 75%, we would have data from 375 individuals per group at 12 months. According to results from the WASBIRT study, the frequency distribution of number of days drugs were used in the past 30 days follows a Poisson distribution. For individuals who received a BI in WASBIRT, at baseline, average days of drug use in the past 30 days were 3.8 for moderate risk users, 7.0 for high risk users who received only a BI, and 8.7 for high risk users who received a BI and brief therapy and/or chemical dependency treatment. Based on these averages, the study would have 89% power to detect as low as a 2.5% reduction in average drug use days for moderate risk users, at a two-sided alpha level of .05, and an R^2^ between BI indicator variable and other covariates of .25. If the R^2^ between the BI indicator variable and other covariates were 0.5 (a conservative assumption), the power to detect as low as a 2.5% reduction in average drug use days for moderate risk users is 74%; the power to detect a 5% reduction in average drug use days is 99%. For high risk users, the power to detect a reduction in drug use of at least 2.5% is higher. The end-status analysis assumed for these power calculations is considerably conservative, as data from earlier points in time are not used. Thus, the proposed study has sufficient power to address the first two specific aims.

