### Choosing the primary outcome variables

Outcome variables were selected specific to each of the study’s aims:

#### Aim 1

For the first aim—to examine whether BI is effective at improving drug use, psychiatric outcomes, select psychosocial outcomes, and attendance in drug abuse treatment—it is important to reliably capture changes in drug use as well as in other variables in as brief a period of time as possible. Because of its widespread use, brevity, and reliability, the validated short form of the Addiction Severity Index (ASI), the ASI-Lite [55], was selected for this purpose along with the Treatment Services Review (TSR) [56]. To further minimize time burden on participants, we only administer items required to compute the ASI composite scores (half the total items) [55].

In order to identify changes in illicit drug use, we use items from the ASI drug section to measure days of any drug use. A urine toxicology screen is used to supplement participants’ responses. In addition, we use the ASI composite scores as comprehensive measures of participants’ medical, psychiatric, legal, family/social, and employment status. The HIV Risk-Taking Behavior Scale is used to assess risk-taking behavior among intravenous drug users [57] and the EQ-5D-3L is used to measure health status [58]. Administrative data are used to supplement ASI data on legal (e.g., arrests) effects. Changes in attendance in drug treatment are obtained from the TSR as well as from state administrative chemical dependency treatment records.

#### Aim 2

The second aim—to test whether fidelity to the BI model is associated with better outcomes—requires a reliable way to assess fidelity. Because of is reliability, cost effectiveness, and brevity, the MITI, which provides a standardized way to rate session audiotapes for degree of MI content, was selected for this purpose [47]. Outcomes for this aim include changes in illicit drug use and drug treatment attendance as measured in the first aim.

#### Aim 3

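### The stated 89%, 74% and 99% power belongs to a 12-month Poisson regression, not to the planned linear mixed model, and does not follow from the stated inputs

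*Protocol article*

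**What the plan says.** All references are to the protocol article.

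- **Power analysis, outcome and time point:** "For the primary outcome of drug use reduction, we computed power for the last point in time when data are collected from participants".
- **Power analysis, distribution:** relying on an earlier study, it says that "the frequency distribution of number of days drugs were used in the past 30 days follows a Poisson distribution". The baseline mean used is "average days of drug use in the past 30 days were 3.8 for moderate risk users".
- **Power analysis, result:** "the study would have 89% power to detect as low as a 2.5% reduction in average drug use days for moderate risk users". This figure takes an R-squared of 0.25 for the BI indicator on the covariates, and the test is set "at a two-sided alpha level of .05". With an R-squared of 0.5 it gives 74% for a 2.5% reduction and 99% for 5%. The analysable sample is 375 per group (75% of 500). The section adds that an end-status calculation is conservative because earlier visits are unused, and concludes that power is sufficient for the first two aims.
- **Data analysis:** "Time trend models will be used to examine temporal effects", with time categorical over baseline, 3, 6, 9 and 12 months, and "analyses will be conducted with linear mixed models". Clinics are fixed effects and interventionists random. No count model is mentioned.
- **Outcomes:** the heading is plural, "Choosing the primary outcome variables". Under Aim 1 it covers drug-use days, ASI composites, the HIV risk scale, EQ-5D-3L and treatment attendance, and does not single one out. The power section speaks of one primary outcome.

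**The concern.** The article states two models for the same outcome, and they are not compatible. The powered model is a Poisson regression at one visit, with the effect as a relative reduction. The planned model is Gaussian over five assessments, with the effect as a difference in days. Power calculated for the first is not power for the second.

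The size of the power claim also calls for a check. A 2.5% reduction from 3.8 days is 0.095 day per month, and 375 patients per arm are said to detect it almost nine times in ten. If that is wrong, the trial has little chance of detecting the effect it names, a null result would be read as stronger evidence against brief intervention than it is, and the conclusion of sufficient power has no support under either model.

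**Working it through.** **Inputs (Power analysis section).** N = 2 × 375 = 750; 1:1 allocation, so p = 0.5; mean μ = 3.8 days per 30 days; rate ratio RR = 0.975 or 0.95; R² = 0.25 or 0.5; two-sided alpha 0.05, z = 1.96.

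**Formula.** The usual power for a Poisson regression with one binary covariate is

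power = Φ{[√(N·T·μ·(1−R²))·|ln RR| − z·√V0] / √V1},

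with V0 = 1/(p(1−p)) = 4 and V1 = 1/(1−p) + 1/(p·RR). V1 is 4.051 for RR = 0.975 and 4.105 for RR = 0.95. T is the exposure per patient in the time unit of μ. Because 3.8 is already a count per 30 days, T = 1.

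**Step 1: the stated inputs, T = 1.**
- 2.5%, R² 0.25: √(750 × 3.8 × 0.75) × 0.02532 = 1.171; (1.171 − 3.920)/2.013 = −1.366; power 8.6%.
- 2.5%, R² 0.5: 0.956; −1.473; power 7.0%.
- 5%, R² 0.5: 1.936; −0.979; power 16.4%.

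The article states 89%, 74% and 99%.

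**Step 2: what reproduces the stated figures.** Of the combinations tried (N of 375, 750 and 1,000; one- and two-sided; T of 1 and 30), only N = 750, two-sided, T = 30 matches the article.

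| Reduction, R² | Stated | T = 1 | T = 30 |
|---|---|---|---|
| 2.5%, 0.25 | 89% | 8.6% | 89.2% |
| 2.5%, 0.5 | 74% | 7.0% | 74.3% |
| 5%, 0.5 | 99% | 16.4% | 99.95% |

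This confirms that a Poisson regression was powered. It also indicates that the 30-day mean was entered as a daily rate over 30 days, that is 3.8 × 30 = 114 drug-use days in a 30-day window. The information is inflated 30-fold.

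**Step 3: detectable reduction under pure Poisson variance.** Solving the T = 1 formula for 80% power gives about 10%, 12% and 14% at R² of 0, 0.25 and 0.5.

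**Step 4: the planned type of model.** Take a linear comparison of 12-month means, 375 per arm, no covariates, difference δ = 0.025 × 3.8 = 0.095 day:

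SE = SD × √(2/375); power = Φ(δ/SE − 1.96) + Φ(−δ/SE − 1.96); difference detectable at 80% power = 2.80 × SE.

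The article gives no SD. √3.8 = 1.95 is what a Poisson count implies; the other values are assumptions.

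| SD (days) | Power for 2.5% | Detectable at 80% |
|---|---|---|
| 1.95 | 10.2% | 0.40 day (10.5%) |
| 4 | 6.2% | 0.82 day (21.5%) |
| 8 | 5.3% | 1.64 days (43%) |
| 10 | 5.2% | 2.05 days (54%) |

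**Step 5: does using all visits rescue it?** Averaging four follow-up visits multiplies the variance by (1 + 3ρ)/4. With an assumed correlation ρ of 0.3 to 0.7, power for 2.5% at SD 1.95 is 16% to 12%. At SDs of 6 to 8 it stays at 5% to 6%.

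**The case against.** The strongest reply has four parts.

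- **The difference in visits is disclosed.** The power section says that it ignores earlier visits and calls this conservative. That stands, and powering a simpler end-point comparison is not an error in itself. But the remark covers only the use of visits, not the distribution or link, and Step 5 shows that the extra visits do not close the gap.
- **A linear mixed model is not invalid here.** With about 375 per arm it can give an approximately valid mean difference at 12 months, and 2.5% can be expressed as 0.095 day. That also stands. A reader might infer that no valid result could decide Aim 1; the article does not support this, because the power section singles out drug use and the 12-month visit.
- **The plural heading does not create a rule that any outcome can win.** The section says only that outcomes were chosen by aim. A reader might count nine Aim 1 measures and derive a family-wise error of 1 − 0.95⁹ = 37%. No such success rule is stated, and the measures are unlikely to be independent. The exact contrast and multiplicity rule may properly sit in the full plan. What remains is an inconsistent label.
- **Some inferences lack a source.** The article reports no share of zero counts; its own Poisson assumption implies about 2% (e^−3.8). Nor does it say that deaths will enter a linear mixed model: that model is justified by repeated assessments, whereas deaths come from administrative records.

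None of this explains how the three stated powers follow from the stated inputs, or why an outcome described as Poisson is assigned a linear model.

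**Conclusion.** The concern holds in this form. The article gives a Poisson power for an analysis that it plans as a linear mixed model, and the figures are not reproducible from its inputs: about 9%, 7% and 16% instead of 89%, 74% and 99%. For the linear comparison, power for a 2.5% reduction is about 10% at best at 12 months. The stated conclusion of sufficient power is therefore unsupported under either model.

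The Poisson figures rest only on the article's inputs and a standard formula. That a 30-fold exposure was entered is an inference from the match; the article does not mention it. The linear figures rest on assumed SDs above 1.95 and assumed correlations. The Poisson figures are probably optimistic: they give all 750 patients the moderate-risk mean, while the article quotes means from 3.8 to 8.7 across risk groups, and such mixing alone pushes the variance above the Poisson value. Higher means do not rescue the claim: at 7.0 and 8.7 days, with R² 0.25, power for 2.5% is 12% and 14%.

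This should be corrected. It does not make the trial's primary comparison invalid.

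**What to change.** 1. **Model.** Analyse drug-use days in the past 30 days with a log-link count mixed model over all visits that allows extra-Poisson variance (negative binomial, or quasi-Poisson with robust standard errors). Name the 12-month BI/ECAU ratio as the primary contrast, two-sided 5%. This puts the analysis on the relative scale of the power section.
2. **Power.** Withdraw the 89%, 74% and 99%. Restate power, or the detectable reduction, for that test with the 30-day mean counted once. Pure Poisson variance gives about 12% at 80% power and R² 0.25. Show how this grows over a stated range of overdispersion, and revise the conclusion of sufficient power accordingly.
3. **Labels.** Align the plural outcome heading with the single primary outcome in the power section by labelling the other Aim 1 measures secondary.

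The cost is small: a change of model, a new power calculation, a less favourable power figure, and loss of primary status for the other measures. No data collection changes.

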### Defining the population

As stated earlier, the population of interest is individuals seeking primary care treatment in a safety net medical center setting. Screening procedures are designed to identify individuals with problem drug use along a continuum of severity. Study inclusion criteria include adults age 18 and over; having used an illegal drug or used a prescription medication for nonmedical reasons at least once in the past three months [24] (equivalent to a DAST-10 score greater than 0 [25,26]); currently receiving care in the primary care clinic and planning to continue such care for the next year; English speaking and able to read and understand screening and assessment forms (6^th^ grade literacy); and having a phone, easy access to a phone with voicemail, or access to e-mail in order to facilitate scheduling.

To enhance external validity there are few baseline exclusion criteria. They include having attended formal treatment for substance abuse (excluding self-help groups such as Alcoholics Anonymous) in the past month; life-threatening medical illness (potential mortality in next year); severe cognitive impairment or active psychosis interfering with cognitive ability to process the BI (based on performance during consent and assessment); or active high risk suicidality [27].

There are two reasons for not excluding patients with the most severe drug problems from this trial. First, although some studies of BI for alcohol have found that patients with alcohol dependence responded less well to a BI than patients with less severe abuse or hazardous drinking, Field recently found that patients with alcohol dependence responded better to a BI than those with less severe problems [28] and Cobain found hospital-based BI effects to be independent of baseline dependence or medical comorbidity [29]. Second, even if a BI were inadequate as a stand-alone treatment for safety net patients with severe drug dependence, BI may prove to be a valuable referral mechanism for getting these patients to more intensive chemical dependency treatment, as it did in WASBIRT [30]. For these reasons, we include individuals across the full range of drug use and abuse in the present study. To balance drug use severity across BI and control groups, we use the DAST-10 score as a stratifying variable.

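### The power quoted for moderate risk users counts all 750 analysed patients, and it rests on a Poisson variance that cannot hold for the pooled sample

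*Protocol article*

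**What the plan says.** The Power analysis section expects 500 patients enrolled per group and, at 75% response, 375 per group with 12-month data. It takes the outcome's distribution from WASBIRT: "the frequency distribution of number of days drugs were used in the past 30 days follows a Poisson distribution". No SD or variance is given. The baseline means, also from WASBIRT, are "3.8 for moderate risk users, 7.0 for high risk users who received only a BI, and 8.7 for high risk users" with further therapy or treatment.

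Three power figures follow, all two-sided at 0.05:
- With R² of 0.25 for the treatment indicator on the covariates, "the study would have 89% power to detect as low as a 2.5% reduction in average drug use days for moderate risk users".
- With R² of 0.5, "the power to detect as low as a 2.5% reduction in average drug use days for moderate risk users is 74"%.
- Also with R² of 0.5, "the power to detect a 5% reduction in average drug use days is 99"%.

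The section then adds: "For high risk users, the power to detect a reduction in drug use of at least 2.5% is higher". It concludes that power is sufficient for the first two aims.

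On who is enrolled, the section Defining the population says: "we include individuals across the full range of drug use and abuse in the present study". One use in the past three months is enough to enter, and the most severe users are not excluded. DAST-10 severity is a stratification factor. The Data analysis section plans linear mixed models for BI versus ECAU in the whole randomised sample.

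**The concern.** The first problem is the sample. Power is stated for one risk group, yet the only sample size given is the total over all risk groups. If the total was used, the figure describes a trial made up entirely of moderate risk users, which is not this trial. The statement about high risk users then uses the same patients again.

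The second is the variance. A Poisson outcome has variance equal to its mean, so the mean alone sets the standard error. The outcome here is a count from 0 to 30 days in a population that runs from occasional use to severe dependence. If the true spread is wider, the standard error is too small and the power too high.

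What is at stake is how the result is read. A null finding from this policy trial would be judged against a claimed ability to detect a 2.5% reduction.

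**Working it through.** **Inputs from the article.** N = 750 (375 per group); two-sided alpha 0.05; mean mu = 3.8 days per 30 days for moderate risk, 7.0 and 8.7 for the two high risk groups; R² = 0.25 or 0.5; reduction 2.5% or 5%. **Assumed, because not given:** the share of moderate risk users, the mix of the three groups, and the SD within groups.

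**Formula.** Standard Poisson-regression power for a 1:1 binary covariate, with b = ln(1 − reduction), exposure T and variance/mean ratio phi:

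power = Phi{ [ sqrt(N·T·mu·b²·(1 − R²)/phi) − 1.96·2 ] / sqrt(2 + 2/exp(b)) }

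**Step 1: reproduce the stated figures.** For a 2.5% reduction, b = −0.02532 and the denominator is 2.013. With N = 750, T = 30, phi = 1 and R² = 0.25, the square root is 6.411, so z = (6.411 − 3.920)/2.013 = 1.238 and power is 89.2%. With R² = 0.5, power is 74.3%; for a 5% reduction it is above 99.9%. All three stated figures are met. Of the variants tried (N = 375, 750, 1000; T = 1 and 30; mean 3.8 and 3.8/30; one- and two-sided), only this one meets them all. T = 30 is a separate error, because 3.8 is already days per 30 days. With T = 1 the three powers are 8.6%, 7.0% and 16.4%.

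**Step 2: the number of moderate risk users.** Keep the article's method, including T = 30, and change only N:

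| Moderate risk users among the 750 | R² = 0.25 | R² = 0.5 |
|---|---|---|
| all, 750 | 89% | 74% |
| half, 375 (assumed) | 62% | 46% |
| one third, 250 (assumed) | 46% | 33% |

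These show the effect of N alone; with T = 30 they are not valid powers. Now set T = 1 and solve for the reduction detectable at 80% power with mu = 3.8:

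| N | R² = 0.25 | R² = 0.5 |
|---|---|---|
| 750 | 11.5% | 13.9% |
| 375 | 16.0% | 19.2% |
| 250 | 19.2% | 23.1% |

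**Step 3: high risk users.** By the article's method (T = 30, R² = 0.25), the 7.0-day group has 71% power with 250 patients and 87% with 375, both below 89%. Matching 89% takes 750 × 3.8/7.0 = 407 patients at mean 7.0, or 750 × 3.8/8.7 = 328 at mean 8.7. Power is automatically higher only if the same 750 are counted again.

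**Step 4: one Poisson for the pooled sample.** At mean 3.8 the Poisson SD is sqrt(3.8) = 1.95 days. It puts 2.2% of patients at 0 days and about 1 in 90,000 at 15 or more days. Mix the three quoted means, with an exact Poisson inside each group:
- Equal thirds: mean 6.5; between-group variance (2.7² + 0.5² + 2.2²)/3 = 4.13; total variance 10.63; variance/mean 1.63.
- 60/20/20: mean 5.42; between-group variance 4.23; total variance 9.65; variance/mean 1.78.

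So a Poisson in each risk group and a single Poisson in the pooled sample cannot both be true.

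**Step 5: what that mixing costs the whole-sample comparison.** With N = 750, T = 1, R² = 0.25 and 80% power, the detectable reduction is 11.3% (thirds) and 12.8% (60/20/20), against 11.5% at mean 3.8 with phi = 1. The higher pooled mean offsets the extra variance.

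**Step 6: spread within groups (assumed).** Detectable difference in days = (1.96 + 0.84) × SD × sqrt(2/375). SD 5 gives 1.02 days, SD 7 gives 1.43 and SD 10 gives 2.05. The comparator is 0.44 day (11.5% of 3.8), which includes R² = 0.25; the same simple formula with SD 1.95 gives 0.40 day.

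**The case against.** The strongest reply is that the subgroup wording is loose, not wrong. The Data analysis section plans no analysis by risk group, so the three means may be alternative base rates for the whole sample, with 3.8 the least favourable. On that reading N = 750 is right and higher power at a higher mean follows directly. This is a fair account of what may have been intended, but it is not what the text says: the figures are stated for moderate risk users, in a trial that will not have 750 of them.

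On the variance, a reader might infer that the article contradicts the Poisson form altogether, or that the detectable effect grows by 28% to 33%, the square roots of 1.63 and 1.78. The article does not support either. It gives no variance, and it attributes the distribution to WASBIRT results that are not shown. Eligibility limits show who may enter, not how common heavy use is. The 28% to 33% compares the mixture with a Poisson at the same pooled mean, whereas the article used 3.8; against that, almost nothing is lost (Step 5).

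Two other comparisons should also be avoided. Setting 1.0 to 2.0 days against 0.095 day (2.5% of 3.8) charges the 30-fold exposure error to this point. Dividing 1.0 to 2.0 days by 3.8 puts an all-patient difference over a subgroup mean.

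The reply is also right that the calculation ignores the earlier assessments, as the article says, and that a mixed model with repeated measures may absorb some stable between-patient spread. It is right too that the planned analysis estimates its variance from the trial data. The fault is therefore in the power statement, not in the analysis.

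**Conclusion.** The point holds in a limited form. The power quoted for moderate risk users requires all 750 analysed patients to be moderate risk, which conflicts with enrolment across the full severity range. Under assumed shares of one half to one third, the article's own method gives 62% to 46% instead of 89% (R² = 0.25). With the exposure corrected, the detectable reduction for that group is 16% to 19%, against 11.5% for all 750. The statement about high risk users also lacks a sample size of its own.

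A single Poisson cannot describe the pooled outcome, since the three means alone give a variance/mean ratio of about 1.6 to 1.8. For the whole randomised comparison, this leaves the relative detectable reduction near 11% to 13%. A reader might go on to conclude that overdispersion is shown to make the whole trial much less sensitive. That remains an assumption: wider spread within risk groups is plausible given who is eligible, but the article does not quantify it. If the SD were 5 to 10 days, 375 per arm would detect about 1.0 to 2.0 days at 80% power, against about 0.44 day for the exposure-corrected Poisson calculation.

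**What to change.** When the calculation is rerun without the 30-fold exposure, restate the detectable difference for the comparison actually planned: the whole randomised sample, N = 750, at the pooled mean. Replace the Poisson variance with an empirical SD of 30-day use, from the WASBIRT results if they are available to the investigators, or from this trial's blinded pooled baseline. Use a variance structure that agrees with the linear mixed model in the Data analysis section, and print the SD and N used. Remove the power statements by risk group, or recompute each with the number of patients expected in that group. Then revisit the conclusion that power is sufficient.

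This takes one recalculation and a few sentences. It needs no extra patients and no change to randomisation or analysis. The cost is a less favourable stated figure.
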